### Secondary outcomes for the salt reduction intervention

- The proportion reporting efforts to reduce salt consumption
- The proportion with hypertension
- Mean 24-hour urinary sodium excretion (based on a sub-sample)
- Average daily per capita salt sale volume in the village estimated from salt sale records in the village convenience stores

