### Baseline and follow-up surveys

A baseline and a follow-up random sample survey (2 independent samples) of older adults (50+/60+) will be conducted in all of the 120 villages before and after the interventions. In each village, the survey will collect data from 40 consenting adults, half men and half women. Sampling will be done by the China International Center for Chronic Disease Prevention located in Beijing acoording to village rosters collected before the survey. All age-eligible (50+/60+) villagers will receive a random number. The random numbers will be ranked according to ascending order and informed consents will be sought according to the rank orders until 20 men and 20 women in each village consent to participate in the survey. Efforts to make sure that only one older adult from the same household will be recruited in the survey will be made – through a roster including household information or someone (e.g. village chief) who knows the villagers well enough to identify adults from the same household. Blood pressure, weight, height and heart rate will be measured and recorded according to standardized protocol. A brief questionnaire (see Appendix 2) will be administered by survey staff to collect information on disease history, medication use, care seeking patterns, and lifestyle factors. Survey participants will receive a small gift valued at approximately 5 yuan (RMB) as a token of appreciation for their participation in the survey. Five yuan is approximately half of the minimal wage per hour for hourly workers.

High-risk patients in the evaluation surveys will be defined slightly differently from the high-risk definition in the package. It will be defined as having history of heart disease or stroke; or older age (50+/60+) and having diabetes; or older age (50+/60+) and having a measured systolic blood pressure > 160 mmHg; or older age (50+/60+) and currently on anti-hypertension medication but having ever had a self-reported BP measurement > 160 mmHg. See Appendix 2 for details on identification of high-risk patients from the random sample of older adults.

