**Chief Complaints:**

| **Medical History** |
| --- |
| 1. Does pt have any one of the following diseases (diagnosed in county / higher-level hospitals)？   **CAD**□Yes□No; **Hemorrhagic stroke**□Yes□No; **DM**□Yes□No; **Ischemic stroke**□Yes□No |
| 1. Medications the patient was taking everyday in the past 2 weeks (please record the **name**, **dosage** taken each time, and **times** taken each day, e.g. “Hydrochlorothiazide 12.5mg qd”; if no medication meets the above criteria, please record “NA”). |
| 1. Other medical histories that need to be recorded: |
| **Life Styles** |
| 1. Does the patient take measures to reduce dietary sodium aggressively in everyday life?   □Yes (e.g. do not eat pickled vegetables at all; no MSG and add minimal amount of salt when cooking dishes; unable to eat when the meal is salty.)  □Not so aggressively (e.g. eat some pickled vegetables; take care to reduce salt added in cooking; eat less when the meal is salty.)  □No (e.g. do not pay attention to the amount of salt in food at all.)   1. Is the patient a current smoker？ □Yes □No   If “Yes”, does the patient think about quitting smoking？ □Yes □No   1. Does the patient exercise regularly？(e.g. farming, walking, climbing, etc.)   □Almost everyday □3-5 time/week □1-2 times/week □almost no activities/week |
| **Physical Examination** |
| 1. Blood Pressure (SBP/DBP): / mmHg (This time)   (Optional: / mmHg (Last time), Date: / / (yy/mm/dd)   1. Height: cm; weight: kg; other signs: |
| **Prescription** |
| 1. Referral □Yes □No |
| 1. Therapeutic lifestyle changes (advise the patient to take actions to):   **Reduce salt intake** □Yes □No; **Quit smoking** □Yes □No; **Avoid binge drinking** □Yes □No  **Be physical active** □Yes □No **Control weight** □Yes □No; |
| 1. Pharmaceutical treatment (please record the **name** of the drug, **dosage** taken each time, and **times** taken each day, e.g. “Hydrochlorothiazide 12.5mg qd”; if no drug is prescribed, please record “NA”):   Doctor’s Signature: |

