## APPENDIX 2 – Questionnaire for baseline and follow-up population surveys

**CRHI Survey Questionnaire（2010）**

Hello! My name is . I am a healthcare researcher from (institution). For the purpose of improving health care in your area, we are conducting a health survey to collect information from middle aged or older people in your village. All information collected from this survey will be kept confidential. You are entirely free to decide whether or not to take part in this research study, and there will not be any negative effect to you if you choose not to take part. You are also free to discontinue your involvement with the research study at any time. Thank you for your support and cooperation!

Date (2010/mm/dd) **2010/□□/□□**

Time (hour: minutes) **□□:□□**

| **A. General information** | | | | | | | | | | | | | |
| --- | --- | --- | --- | --- | --- | --- | --- | --- | --- | --- | --- | --- | --- |
| A.1 Name:  A.2 Sex: □1.Male □0.Female  A.3 ID**□□□□□□□□□□□□□□□□□□**  A.4 Years of age  A.5 Years of schooling | | | | | | | | | | | | | |
| **B. Lifestyle information** | | | | | | | | | | | | | |
| B.1 Have you smoked during the past 3 months? (multiple choice)  □1.Yes, cigarette B.1.1 On average, how many cigarettes per day  □2.Yes, tobacco leaf B.1.2 On average, how much “Liang” per day  □3.Other (go to B.2)  □4 No (go to B.2) | | | | | | | | | | | | | |
| B.2 Have you drunk alcohol during the past 3 months? (multiple choice) | | | | | | | | | | | | | |
| □1. Chinese white wine | | | □2. Beer | | | | | | | □0. No  (go to B.3) | | | □3.Other  (go to B. 3) |
| B.2.1How often?  □1. <Once/week  □2. 1-2times/week  □3. 3-5times/week  □4. 1-2times/day  □5. >Twice/day | B.2.2 How much per tima?  □1.<１Liang  □2.1-3 Liang  □3.3-5 Liang  □4.>halt Jin  (note:1Liang=50g≈50ml ;1 Jin=500g≈0.5L) | | B.2.4 How often?  □1. <Once/week  □2.1-2times/week  □3.3-5times/week  □4. 1-2times/day  □5. >Twice/day | | | | | B.2.5 How much per time?  □1.<1bottle  □2.2-5bottles  □3.6-10bottles  □4.>10bottles  (1 bottles=750ml) | |  | | | |
| B.2.3 How many times did you drink alcohol more than half Jin? | | | B.2.6 How many times did you drink alcohol more than 10 bottles? | | | | | | |

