| B.3 Have you done any farming activities during the past 3 months? （30 minutes or above per time）  □1. Almost everyday  □2. 3-5days/week  □3. 1-2days/week  □4. Almost none | | | | | | | B.4 Have you exercised during the past 3 months?  （30 minutes or above per time）  (e.g., waling、running、dancing，Taiqi）  □1. Almost everyday  □2. 3-5days/week  □3. 1-2days/week  □4. Almost none | | | | | | |
| **Physical examination (PE.1). Blood pressure and heart rate measurement (1st)** | | | | | | | | | | | | | |
| PE.1.1 Blood pressure（Systolic/Diastolic）:  PE.1.1.1**□□□**/ PE.1.1.2**□□□** mmHg | | | | | | | PE1.2 Heart rate:  PE.1.2.1**□□□**/minute | | | | | | |
| B.5 How often do you usually eat pickled foods?  □1At least once a day  □23-6 times/week  □31-2 times/week  □4Sometimes  □5Almost none | | | | | | | B.6 How do you do if the food is tasteless when you dine?  □1 Always eat pickle/add soy source/add salt  □2 Sometimes eat pickle/add soy source/add salt  □3Don’t mind | | | | | | |
| B.7 High salt intake will  □1 Bad for health  □2 Good for health  □3 No effect on health  □4 Don’t know | | B.8 Which of the following will reduce blood pressure?  □1Medicine  □2Smoking  □3Est less salt  □4Eat more food | | | B.9 How much daily salt intake is recommended for adults?  □0 Do not eat salt  □1≤ 6 g  □2＞ 6 g  □3 Don’t know | | | | | | | | |
| **C. Disease history** | | | | | | | | | | | | | |
| C.1 Do you have diabetes?  □1. Yes □0.No □9.Don’t know (if No or Don’t know, go to C.2)  D.1.1 Diagnosed by county or higher levels hospitals?  □1. Yes □0. No □9. Don’t know  C.2 Do you have stroke?  □1. Yes □0.No □9. Don’t know　(if No or Don’t know, go to C.3)  C.2.1 Diagnosed by county or higher levels hospitals?  □1. Yes □0. No □9. Don’t know  C.2.2 Ischemic stroke or hemorrhagic stroke?  □1. Ischemic stroke □2. Hemorrhagic stroke □3. Don’t know  C.3 Do you have coronary heart disease?  □1. Yes □0. No □9. Don’t know (if No or Don’t know, go to C.4)  C.3.1 Diagnosed by county or higher levels hospitals?  □1. Yes □0. No □9. Don’t know  C.3.2 Had electrocardiograph evidence of CHD?  □1. Yes □0. No　 □9. Don’t know  C.4 Do you have hypertension?  □1. Yes □0. No □9. Don’t know  C.4.1 How many years have you had hypertension? Years □9. Don’t know  C.5 Have you had your blood pressure measured after age 50 (male)/60 (female)?  □1. Yes □0.No □9. Don’t know (if No or Don’t know, go to C.6)  C.5.1 Please provide the highest systolic blood pressure **□□□**mmHg | | | | | | | | | | | | | |

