| C.6 During the past 12 months, did you see your village doctor once a month?  □1. Yes  □0. No | | | | | | | | | C.7 Does your village doctor measure your blood pressure during visits?  □1. Never see village doctor  □2. Never measure  □3. Sometimes(occasionally)  □4. Almost every time  □5. Every time | | | | |
| **Physical examination (PE.2). Blood pressure and heart rate measurement (2nd)** | | | | | | | | | | | | | |
| PE.2.1 Blood pressure（Systolic/Diastolic）  PE.2.1.1**□□□**/ F.1.2**□□□** mmHg | | | | | | PE.2.2 Heart rate:  PE.2.2.1**□□□**/minute | | | | | | | |
| **Physical examination (PE.3). Body height and weight measurement** | | | | | | | | | | | | | |
| PE.3.1 Height **□□□.□** cm | | | | | | PE.3.2 Weight **□□□.□**kg | | | | | | | |
| | **CL．CVD high-risk patient confirmation checklist (CL) by the interviewer** | | | --- | --- | | CL.1 Have confirmed diabetes（C.1.1 answer Yes） | □1.Yes □0.No | | CL.2 Have confirmed stroke（C.2.1 answer Yes） | □1.Yes □0.No | | CL.3 Have confirmed CHD（Both C.3.1 and C.3.2 answer Yes） | □1.Yes □0.No | | CL.4 Have reported SBP at older age ≧ 160mmHg （C.5.1） | □1.Yes □0.No | | CL.5 Twice systolic measurements ≧160mmHg （PE.1.1 and PE.2.1） | □1.Yes □0.No | | **If any of the above is ticked YES, go to D section; otherwise, end survey** | | | | | | | | | | | | | | | |
| **D. Medication use and medical care (high-risk patients ONLY)** | | | | | | | | | | | | | |
| D.1 When was the last time that you saw your village doctor for your heart disease, stroke, diabetes or hypertension problem(s)? days ago  During that visit, did village doctor provide the following recommendations?  D.1.1 Reduce salt intake □1.Yes □0.No  D.1.2 Quit smoking □1.Yes □0.No  D.1.3 Avoid binge drinking □1.Yes □0.No  D.1.4 Be physically active □1.Yes □0.No  D.1.5 Control weight □1.Yes □0.No | | | | | | | | | | | | | |
| D.2 During the past 12 months, due to your heart disease, stroke, diabetes or hypertension problem(s)  D.2.1 How many times have you been in hospital?  （if no，go to D.3）  D.2.2 How many days have you been in hospital?  D.2.3 How much have you spent for hospitalization? RMB | | | | | | | | | | | | | |

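### The salt secondary outcome on reported efforts to cut salt has no matching question in the village survey, so as printed it cannot be compared across the planned 60 vs 60 villages

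*Protocol*

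**What the plan says.** The section on secondary outcomes for the salt reduction intervention opens its list with "The proportion reporting efforts to reduce salt consumption". It names neither the instrument nor the population.

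The section on baseline and follow-up surveys describes how individual data are collected in all 120 villages: "A brief questionnaire (see Appendix 2) will be administered by survey staff". Appendix 2 is headed "Questionnaire for baseline and follow-up population surveys", so one form is printed for both rounds. Its salt-related content is:

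- "B.5 How often do you usually eat pickled foods"
- "B.6 How do you do if the food is tasteless when you dine"
- three knowledge items, B.7 to B.9, ending with "B.9 How much daily salt intake is recommended for adults"
- in section D, which only high-risk respondents answer, "During that visit, did village doctor provide the following recommendations", where less salt is one of the listed recommendations (D.1.1).

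A direct question on effort is found in Appendix 1-B, the case management record: "Does the patient take measures to reduce dietary sodium aggressively in everyday life". It is asked at the initial visit and again as an optional six-monthly item. Each follow-up page also has a tick box on whether the patient has been trying to eat less salt. The sections on outcomes evaluation and case management records confine this record to the package arm: 60 villages, high-risk patients. The outcomes evaluation section also requires outcome assessment to be identical in every village, whatever its allocation.

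**The concern.** An outcome about what people report trying to do needs a question that asks them. The survey instrument is fixed in this protocol, and no item in it does so. Three routes then remain, none of them satisfactory: the outcome is dropped; a habit or knowledge item is substituted once data are in hand; or the outcome is taken from the case management record. The record exists only where the package was randomized, and patients enter it after randomization because a village doctor identified them. Under Appendix 1-C that doctor can also be paid for patients recorded as both cutting salt and not smoking.

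Timing matters as well. The two survey rounds are independent samples, and the project timeline puts baseline in September to October 2010. A question missing at baseline cannot be recovered later.

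**Working it through.** No power or error-rate figure is involved. The check is a reading of the items followed by a count of villages.

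**Inputs.** Randomization section: 120 townships, 30 in each of the four factorial cells. Study design: one village per township. Survey section: 40 respondents per village per round, so 120 × 40 = 4,800 per round.

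**Step 1. Does any survey item measure effort?**

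| Appendix 2 item | Asked of | What it records |
|---|---|---|
| B.5 | all | how often pickled food is eaten (habit) |
| B.6 | all | what is done with bland food (habit or taste) |
| B.7 to B.9 | all | knowledge |
| D.1.1 | high-risk only | advice given by the doctor |

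No other item in sections A to D concerns salt. Respondents asked about effort: 0 of 4,800 per round. By contrast, several package secondary outcomes do have a survey item: lifestyle advice (D.1), antihypertensive use (D.3) and aspirin (D.4).

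**Step 2. Where is effort recorded?** Only in the case management record. Villages holding it, by cell:

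| | Salt | No salt |
|---|---|---|
| Package | 30 of 30 | 30 of 30 |
| No package | 0 of 30 | 0 of 30 |
| Total | 30 of 60 | 30 of 60 |

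**Step 3. Which comparisons are possible?** The planned salt comparison is (30 + 30) vs (30 + 30) = 60 vs 60 villages. From the survey it cannot be made. From the record, a 30 vs 30 comparison (both interventions vs package only) is possible, restricted to high-risk patients whom doctors identified. Salt only vs usual care has no data. The salt primary outcome is set in older adults generally, a wider population than the record covers.

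**Step 4. What does timing change?** The analysis plan compares post-intervention levels and, in addition, net pre-post differences. With an effort item from baseline onward, both can be done. With the item at follow-up only, the first can be done and the second cannot. With no item, neither can be done from the survey.

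**The case against.** Several points can fairly be made on the other side.

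- **B.5 and B.6 could serve.** They are self-reported salt behaviours asked in every village, and the record's own item illustrates its answers with pickled vegetables and salt added in cooking. As proxies they are reasonable. But the protocol does not define the outcome from them, and they do not separate effort from taste: someone who never liked pickles scores well without trying. Choosing a proxy after data collection invites selective reporting.
- **This can be left to the statistical analysis plan.** Such a plan can map an outcome to items. It cannot supply an answer nobody was asked for.
- **Details are deferred.** The section on amendments and additional submissions postpones the salt intervention, process evaluation and other components. The survey questionnaire is not on that list. The planned villager interviews and focus groups are aimed at key stakeholders at the end of the intervention, not at the survey sample.
- **Better salt measures exist.** This stands. The same list includes 24-hour urinary sodium and village salt sales, which limits the damage.

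Stronger readings are tempting but not supported. A reader might infer that salt and control villages cannot be compared at all. The 30 vs 30 record comparison exists, weak as it is. A reader might infer that the sponsor means to use the paid records. Nothing says so, and the payment requires salt reduction and no smoking together, after a 60% regular management rate is reached. A reader might infer that omission at baseline is fatal. The printed form carries 2010 dates and must be reissued for the follow-up round, so an item could be added then and the post-intervention comparison kept.

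Nor should the record's coverage be put at about 10% of older adults (20% high-risk × half managed, from the power section). The consent section expects 10,000 managed patients in 60 villages. That is 10,000 / 60 ≈ 167 per village, or about 11% of all residents of an average village of 1,500, which implies a larger share of older adults.

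**Conclusion.** The point holds in a limited form. As printed, this salt secondary outcome cannot be obtained from the survey or compared across the planned 60 vs 60 villages. Using the case management record instead would reach only 30 of 60 villages on each side, within the package stratum and among high-risk patients identified by doctors. It would also contradict the protocol's own rule of identical assessment in every village.

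The conclusion rests on Appendix 2 being the form fielded as printed, and on the outcome meaning effort rather than habit, knowledge or advice received. The cell counts follow from the randomization scheme and do not depend on how many patients are managed. One of four salt secondary outcomes is affected. The change should be made because it is cheap and the baseline opportunity is limited in time.

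**What to change.** Before the baseline survey:

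- Add one item to section B of Appendix 2, asked of all 40 respondents in every village, on whether the person has been trying to eat less salt. Adapt the Appendix 1-B wording, which is written for a doctor reporting on a patient.
- Define the secondary outcome from that item, naming the population and fixing in advance which answers count as effort.
- State that case management records are not a source for this outcome.
- Use the same item unchanged in the follow-up form.

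If baseline fieldwork has already passed, add the item at follow-up and state that this outcome will have a post-intervention comparison only.

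The cost is one questionnaire line, with no change to sampling, randomization or the primary outcome.

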### Exploratory outcomes

A series of exploratory outcomes will be assessed including fatal and non-fatal cardiovascular events and all-cause mortality.

## OUTCOMES EVALUATION

The methods used to collect the data for outcome assessments will be basically the same for both interventions except urinary sodium excretion (salt reduction only) and case management records (package only). All outcome assessments will be done in exactly the same way in every village, regardless of its assignment to intervention or control.

### Baseline and follow-up surveys

A baseline and a follow-up random sample survey (2 independent samples) of older adults (50+/60+) will be conducted in all of the 120 villages before and after the interventions. In each village, the survey will collect data from 40 consenting adults, half men and half women. Sampling will be done by the China International Center for Chronic Disease Prevention located in Beijing acoording to village rosters collected before the survey. All age-eligible (50+/60+) villagers will receive a random number. The random numbers will be ranked according to ascending order and informed consents will be sought according to the rank orders until 20 men and 20 women in each village consent to participate in the survey. Efforts to make sure that only one older adult from the same household will be recruited in the survey will be made – through a roster including household information or someone (e.g. village chief) who knows the villagers well enough to identify adults from the same household. Blood pressure, weight, height and heart rate will be measured and recorded according to standardized protocol. A brief questionnaire (see Appendix 2) will be administered by survey staff to collect information on disease history, medication use, care seeking patterns, and lifestyle factors. Survey participants will receive a small gift valued at approximately 5 yuan (RMB) as a token of appreciation for their participation in the survey. Five yuan is approximately half of the minimal wage per hour for hourly workers.

High-risk patients in the evaluation surveys will be defined slightly differently from the high-risk definition in the package. It will be defined as having history of heart disease or stroke; or older age (50+/60+) and having diabetes; or older age (50+/60+) and having a measured systolic blood pressure > 160 mmHg; or older age (50+/60+) and currently on anti-hypertension medication but having ever had a self-reported BP measurement > 160 mmHg. See Appendix 2 for details on identification of high-risk patients from the random sample of older adults.

Because this is a cluster-randomized trial, it is not hard to outcome assessors to know the randomized allocation of the villages. However, standardized quality control procedures (such as independent reviews of the survey questionnaires and 10% audits) will be followed to ensure that survey personnel conduct the survey in an objective manner. Measurement of blood pressure will be done by an electronic device with recording functions to minimize the possibility of any tampering of the readings by study personnel. A systematic plan for quality control and assurance including the surveys and other components will be formulated and included in a separate document on the standard operation procedures for the study (a summary of which will be included in the protocol).

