## OUTCOMES

The primary outcomes will be the same for the package intervention and the salt reduction intervention, which is the mean blood pressure changes between the groups..

The primary outcome for the package intervention will be mean blood pressure level of high-risk patients.

The primary outcome for the salt reduction intervention will be mean blood pressure level of older adults (50+/60+).

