## APPENDIX 1 – Detailed Description of the CVD Prevention and Management ‘Package’

The intervention package will be based upon the application of the core strategies described in the national clinical guidelines for hypertension and cardiovascular disease management in China, with adaptation to ensure the interventions are practical and affordable in rural China. Broadly the package will encourage the identification of a set of high-risk individuals and then seek to improve their clinical management through the application of simplified guidelines and a defined follow-up schedule. This will be achieved by training the primary care providers in the selected villages and supplying an automated electronic sphygmomanometer to each village clinic. The package also includes built-in performance evaluation and feedback mechanisms and a simple performance-based provider payment scheme.

The initial training of the village doctors is considered the beginning of the intervention. Identification and management of high-risk patients will be on a continual basis and last for 2 years (and hopefully will continue even after the end of the study). Therefore, the duration of intervention is 2 years.

*Identification of individuals at high cardiovascular risk* - The package will focus attention on patients considered at high cardiovascular risk on the basis of their falling into one of the following three groups, regardless of current medication use:

- Physician-diagnosed history of coronary heart disease, ischemic stroke, or hemorrhagic stroke, or
- Older age (50 years or older for men; 60 years or older for women – “50+/60+” hereafter) and having physician-diagnosed Type I or type II diabetes
- Older age (50+/60+) and SBP 160 mmHg

These individuals will be identified by training the primary care provider to take a brief medical history and measure blood pressure in all patients 50+/60+. This will be done opportunistically when patients visit the village healthcare clinics for any reason. In addition, the primary care providers will be encouraged to seek out all patients known to have previously suffered from cardiovascular disease using their knowledge of the community and the connections that they have within it. The more time-consuming and costly approach of screening all adults will not be done because it would not be sustainable.

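### Entry to the package's high-risk primary group is decided after the intervention, by factors the package changes and under two differing definitions, so the comparison may be biased in either direction

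*Protocol*

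**What the plan says.** The Outcomes section states: "The primary outcome for the package intervention will be mean blood pressure level of high-risk patients". Under Baseline and follow-up surveys, the data come from "A baseline and a follow-up random sample survey (2 independent samples) of older adults (50+/60"+), so high-risk status at follow-up is assigned when the intervention is over (October 2010 to October 2012, with follow-up surveys from November 2012).

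That section gives these routes into the group:
- history of heart disease or stroke, or diabetes at the qualifying age;
- "older age (50+/60+) and having a measured systolic blood pressure > 160 mmHg";
- "older age (50+/60+) and currently on anti-hypertension medication but having ever had a self-reported BP measurement > 160 mmHg".

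It refers the reader to Appendix 2 for details. There, one checklist item reads "Have reported SBP at older age ≧ 160mmHg" and carries no medication condition. The next item needs both survey readings at the threshold. The reported value comes from "C.5.1 Please provide the highest systolic blood pressure", which is undated and is skipped if pressure was never measured at the qualifying age.

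Appendix 1 trains package doctors to "take a brief medical history and measure blood pressure in all patients 50+/60"+, opportunistically at clinic visits. It adds measurement at every visit and prescribing for high-risk patients. Appendix 1-C pays per patient identified. Control villages continue usual practice.

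**The concern.** Randomisation makes the villages comparable. It does not do so for a subgroup chosen afterwards by variables that the treatment moves. Three of these are in play: survey-day SBP is the outcome itself, current medication is what the package promotes, and the highest known SBP depends on how often pressure was taken. If package villages label more or different people as high-risk, the two high-risk means describe different kinds of people.

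At stake are the package's primary outcome and the package secondary outcomes that use high-risk individuals as denominator. The power section assumes one 20% high-risk share for all clusters.

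**Working it through.** **1. The plan's own yardstick.** Inputs from Statistical power: 8 high-risk people in each of 120 clusters, so 480 per arm; SD 15; intra-cluster correlation 0.05; target 2.5 mmHg. Two-sided testing is assumed.
- Design effect: 1 + (8 - 1) × 0.05 = 1.35.
- Effective n per arm: 480 / 1.35 = 355.6.
- SE of the post-intervention difference: √(2 × 15² / 355.6) = 1.125 mmHg.
- Power at 2.5 mmHg: Φ(2.5/1.125 - 1.96) = Φ(0.26), about 60%.

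The stated figure of more than 90% is not reproduced. That is a separate matter; here only the SE is used.

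**2. Simulation with no effect on blood pressure (1,000,000 people per arm and setting).** Only the chance of having been measured, the number of past readings and the treated share differ by arm. The documents do not give most of these inputs. Assumed ranges: mean SBP 135-145, SD 15-20, within-person SD 8-10, disease or diabetes history 8-12%; control 50% measured with 3 readings, package 50-80% with 3-10. Treated share is 13-31% in control (background and pilot figures) and 50% in package (the share assumed managed in Statistical power).

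| Comparison (package minus control) | Difference, mmHg |
|---|---|
| Survey-section definition, all settings | -3.4 to +1.7 |
| Same, control high-risk share 19-21% | -2.7 to +0.3 |
| Appendix 2 checklist, all settings | -3.6 to +1.6 |
| Detection and treatment equal in both arms | 0 |
| All older adults | within 0.06 of 0 |

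**3. One setting in full.** Mean 140, SD 20, within-person SD 10, history 8%; 50% measured with 3 readings and 30.6% treated (control) against 80% with 10 readings and 50% treated (package). The high-risk share is 21.2% against 29.3%, and the means are 157.9 against 155.2, a difference of -2.7. The net extra entrants average (29.3 × 155.2 - 21.2 × 157.9) / 8.1 = 148.1 mmHg. That is below the control group's 157.9, so they pull the mean down.

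**4. Why the sign can flip.** The mean falls if extra entrants lie below the existing group mean and rises if they lie above it. A larger disease-history share or a smaller SD lowers the existing group mean. Example under the checklist: mean 140, SD 15, within-person SD 8, history 12%, package 80% measured with 3 readings. The share goes from 22.8% to 26.0% and the mean from 149.6 to 150.0. Extra entrants average (26.0 × 150.0 - 22.8 × 149.6) / 3.2, about 153 mmHg, and the mean rises.

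A second set started from usual SBP mean 138 and SD 19, within-person SD 9, history 6%, 40% measured with 1-2 readings in control and 60-80% with 4-8 in package. It gave -1.1 to -2.1 (survey section) and -1.6 to -2.6 (checklist). Changing its assumptions under the survey-section definition:

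| Change | Difference, mmHg |
|---|---|
| History 10% (control share 20.4%) | -0.5 |
| History 12% | -0.2 to 0.0 |
| Total SD 15 | 0.0 to +0.2 |
| Total SD 15 and history 10-12% | +0.8 to +1.8 |
| Package readings 1-2, as in control | -0.3 to -0.5 |

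A lower mean and SD together gave up to +2.3.

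**5. Consequence.** A bias of -2.7 gives 2.7/1.125 = 2.40 SEs, so a two-sided test rejects with probability Φ(2.40 - 1.96), about two in three instead of 5%. A bias of +1.7, if it simply adds, leaves 2.5 - 1.7 = 0.8 mmHg of a true 2.5.

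**6. The pre-post contrast.** Before the intervention both arms are classified by the same process; only the follow-up classification is affected. Subtracting baseline therefore keeps the whole bias. The SE becomes 1.125 × √2 = 1.59 for independent samples, and the rejection rate at -2.7 is still about 40%.

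**The case against.** A reader might infer that the bias always favours the package and amounts to a false benefit of 1 to 2.6 mmHg. The documents do not support that. The sign turns on the disease-history share and the spread of SBP, neither of which is known for this population. The only SD the Protocol gives is 15, and at that value the second set moves to zero or above.

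A reader might also infer that package doctors measure every older villager repeatedly. Appendix 1 limits measurement to clinic attenders and rules out screening all adults. Measurement at every visit applies to high-risk patients only.

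Two further points stand in part. The medication clause keeps treated and controlled patients in the group, which limits losses through falling SBP. It does not make membership independent of arm. Disease and diabetes history is less open to change in two years, which dilutes the problem.

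On the two definitions, the checklist comes before the medication questions in section D, so a medication condition could be applied later from those answers. The difference between above 160 and at least 160 may be a lost symbol, since the sign is missing elsewhere in the Protocol. Neither point settles the matter: nothing says that the condition is applied later, and one measured SBP against two readings is a real difference.

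Mean blood pressure of all older adults is already a package secondary outcome, so an unconditional comparison is planned, though not placed beside the primary one.

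**Conclusion.** The concern holds as a bias of unknown sign and size. High-risk membership at follow-up can depend on arm, and neither the pre-post contrast nor identical survey methods removes this. Over assumed inputs with no blood-pressure effect, the spurious difference runs from about -3.4 to +1.7 mmHg, or +2.3 in the second set. It is near zero in some settings and -2.7 to +0.3 where the control share is close to the Protocol's 20%. Set against a 2.5 mmHg target, it could create or conceal an effect.

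These figures show order of magnitude; they are not estimates for this trial. The rejection rates use SD 15. Simulated high-risk SDs were about 17-21 in the key settings, so actual rates would be somewhat lower. Separately, and needing no simulation, the survey section and Appendix 2 define different primary populations and must be reconciled.

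**What to change.** 1. Write one survey high-risk definition and use it in both the survey section and Appendix 2, stating whether medication is required with the reported SBP, how many readings count, and the inequality.
2. Report the share classified high-risk, and by which route, by arm and survey.
3. Report mean SBP in all surveyed older adults beside the high-risk result as the unconditional comparison. Do not conclude from the high-risk comparison alone that the package lowers blood pressure if the two disagree or the high-risk share differs by arm.
4. Add dates to the follow-up items on diagnosis, highest SBP and start of treatment. Run a sensitivity analysis in people who qualify on facts dated before October 2010.

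Cost: a few questionnaire items and some text. Recalled dates carry error, possibly differing by arm. The sensitivity analysis has fewer patients and omits people undiagnosed before the intervention, whom the package aims to find; for that reason it should not replace the primary definition. The all-adult comparison is diluted: if the effect falls only on a 20% high-risk share, 2.5 mmHg becomes 0.2 × 2.5 = 0.5 mmHg. Agreement should therefore be judged on estimates and confidence intervals, not on whether each test is significant.
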